---

## 1. List of abbreviations

|                |                                                      |
|----------------|------------------------------------------------------|
| AE      | Adverse Event                                        |
| CI      | Chief Investigator                                   |
| CSLD    | Chronic Suppurative Lung Disease                     |
| CXR     | Chest X-ray                                          |
| DSMB    | Data and Safety Monitoring Board                     |
| GCP     | Good Clinical Practice                               |
| HREC    | Human Research Ethics Committee                      |
| IDT     | Institute of Drug and Technology                     |
| Menzies | Menzies School of Health Research                    |
| NHMRC   | National Health and Medical Research Council         |
| NT      | Northern Territory                                   |
| NPA     | Nasopharyngeal aspirate                              |
| NPS     | Nasopharyngeal swab                                  |
| PBMC    | Peripheral Blood mononucleocyte                      |
| QPIDL   | Queensland Paediatric Infectious Diseases laboratory |
| RCT     | Randomized Clinical Trial                            |
| RDH     | Royal Darwin Hospital                                |
| SAE     | Serious Adverse Event/Serious Adverse Experience     |
| SOP     | Standard Operating Procedure                         |
| TTH     | The Townsville Hospital                              |
| WHO     | World Health Organization                            |

## **2. General Information**

### **2.1. Protocol title**

An Intervention study for bronchiolitis in Darwin and Townsville: Improving the management and outcomes for infants hospitalised with bronchiolitis.

### **3. Study Design**

#### **3.1. Hypothesis**

- a) The combined anti-microbial and anti-inflammatory properties of a macrolide, azithromycin, will improve clinical outcomes for infants hospitalised with moderate to severe bronchiolitis.
- b) That co-infection with other respiratory pathogens alters an infant's immune response and is responsible for the differences seen in the clinical recovery of infants with bronchiolitis.

#### **3.2. Aim**

Assess the efficacy of a single dose of Azithromycin (30mg/kg) to

- a) Improve the clinical course of moderate to severe bronchiolitis (assessed by supplemented oxygen requirement and length of hospital stay).
- b) reduce the risk of further respiratory illness within 6 months of this bronchiolitis episode.
- c) Profile the immunopathology of bronchiolitis in the presence and absence of co-existing respiratory infections.

#### **3.3. Significance**

Bronchiolitis is the most common lower respiratory tract infection in infancy. It is primarily caused by infection of the respiratory epithelial cells by Respiratory Syncytial Virus (RSV) although other respiratory viruses including adenovirus, parainfluenza, influenza and human metapneumovirus may also contribute. Bronchiolitis is characterised by extensive inflammation of the lower airways with an associated increase in mucus production and necrosis of epithelial tissue. Clinically, bronchiolitis is manifested by presence of tachypnoea with wheeze and/or crepitations with a preceding upper respiratory illness.

### **3.4 Background and rationale**

#### **3.4.1 Infants with bronchiolitis in the NT: burden and outcomes**

Bronchiolitis (with or without pneumonia) is the most common cause of admission in children aged under 12-months. In a Central Australian study, we described a prevalence of approximately 190 per 1000 children for RSV bronchiolitis. The prevalence of all causes of bronchiolitis would indeed be higher. In our setting, co-existent pneumonia is high in Indigenous children and, at the Royal Darwin Hospital (RDH), the majority of children with bronchiolitis are also treated with antibiotics. The co-existent pneumonia is likely related to the high carriage rate and early acquisition of respiratory pathogens in Indigenous children compared to non-Indigenous children. We have reviewed 100 charts of children hospitalised with bronchiolitis at the RDH and found that the readmission rate of Indigenous children for their next bronchiolitis episode within 6-months was 30% (unpublished). As the majority of these children hospitalised for bronchiolitis are retrieved from remote communities, the impact of the illness and costs plus social dislocation is significant. Furthermore recurrent lower respiratory tract infection is an independent significant risk factor for the later development of bronchiectasis and lower pulmonary function in later years. In addition the severity of the hospitalised episode (oxygen requirement and length of hospital stay) were also risk factors for development of bronchiectasis. In our retrospective chart review we found that Indigenous infants hospitalised with bronchiolitis had more severe bronchiolitis than non-Indigenous infants (unpublished). In Indigenous infants, the severity score at presentation, number of days requiring oxygen and length of hospitalisation were all significantly worse or longer than in non-Indigenous infants ( $p=0.0001$ ,  $0.004$ ,  $0.001$  respectively). Thus any intervention that is efficacious in reducing the

severity of bronchiolitis and/or readmission for bronchiolitis in Indigenous children would be beneficial in both short and long term outcomes.

### 3.4.2 Why use azithromycin for bronchiolitis?

There are 2 published randomised controlled trials on RSV-bronchiolitis with contrasting results. In the Turkish study in hospitalised infants, clarithromycin was effective in reducing the length of hospital stay, severity of illness (oxygen use) as well as readmission rate in infants with moderate to severe bronchiolitis. However in the European based study (primarily from Netherlands), azithromycin was not efficacious in infants hospitalised with bronchiolitis. We suspect that while there are many possible reasons for the difference in efficacy, the major reason for the difference found relates to the setting ie infants in Turkey are more likely to have concomitant bacterial infection compared to the affluent European group. Childhood bronchiectasis remains a problem in Turkey similar to that found in Indigenous children living in the NT. It is highly likely that Indigenous infants in our setting will be similar to that of the Turkish infants. However, it is important to establish whether azithromycin is indeed efficacious in our setting given that extrapolating data from developing countries may result in poorer outcomes.

Bronchiolitis in NT Indigenous children is complicated by the known early colonisation of the nasopharynx by bacterial pathogens, notably *Haemophilus influenzae*, *Moraxella catarrhalis* and *Streptococcus pneumoniae*. Whilst both are macrolides, azithromycin has several benefits over clarithromycin in the Northern Territory setting. Azithromycin is active against a range of respiratory pathogens which colonise NT indigenous infants from a young age (in particular gram negative bacteria including *H. influenzae*). Also azithromycin is currently widely used in the Northern Territory for bronchiectasis, trachoma and sexually transmitted diseases. It has a longer half life and better tissue penetration than clarithromycin, thus requiring a much shorter treatment regime. Once weekly dosing has been shown to be sufficient for tissue effects lasting over a week. As the pharmacodynamic/kinetic properties of azithromycin are superior to clarithromycin, we have elected to use azithromycin rather than clarithromycin.

Macrolides are a family of antibiotics which, in addition to antibacterial properties, possess potent anti-inflammatory properties and also influence bacterial biofilms. Laboratory studies show that macrolides directly dampen airway inflammation by inhibiting the migration of neutrophils to the respiratory epithelium and inhibits further production of pro-inflammatory cytokines and mediators. Given that acquisition and colonisation of respiratory pathogens occur very early in Indigenous infants (as early as 2 weeks) and current data on biofilms present in people with chronic upper respiratory infections, we propose that azithromycin may be a valuable intervention for clinical outcomes of Indigenous infants hospitalised with bronchiolitis.

### 3.5 Flow chart – Intervention arm

[figure not shown]

### 3.6 Study timeline

|                                                       | 2010 |  |  |  | 2011 |  |  |  | 2012 |  |  |  |
|-------------------------------------------------------|------|--|--|--|------|--|--|--|------|--|--|--|
| Recruitment/follow up                                 |      |  |  |  |      |  |  |  |      |  |  |  |
| Microbiology                                          |      |  |  |  |      |  |  |  |      |  |  |  |
| Data analysis, publications, feedback to stakeholders |      |  |  |  |      |  |  |  |      |  |  |  |

## 4 Study Design

All children admitted to the Paediatric ward RDH & TTH with a diagnosis of bronchiolitis will be identified and recorded on the study log. Eligibility of all children will be determined using the eligibility criteria in 4.1. Children enrolled in this study, eligible children not consented and children who do not meet the eligibility criteria will all be recorded on the study log.

### 4.1 Eligibility criteria

| Inclusion criteria           | Exclusion criteria               |
|-------------------------------------|-----------------------------------------|
| Clinical diagnosis of bronchiolitis | Chronic lung disease                    |
| Age 18 months and less              | Macrolide contraindication              |
| Requires supplemental oxygen        | Administered azithromycin within 7 days |
|                                     | Concurrent diagnosis of gastroenteritis |
|                                     | Cyanotic congenital heart disease       |
|                                     | Received O2 longer than 24 hours        |

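### The prior-drug exclusion names azithromycin only, although the protocol credits the tested action to macrolides as a class

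*Protocol*

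**What the plan says.** Section 4.1 lists two exclusions that mention this drug class. One concerns recent use: "Administered azithromycin within 7 days". The other is "Macrolide contraindication", which concerns infants who should not be given a macrolide. It does not address infants who have recently had one.

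The rationale is written at class level. Section 3.1 states: "The combined anti-microbial and anti-inflammatory properties of a macrolide, azithromycin, will improve clinical outcomes". Section 3.4.2 says: "Macrolides are a family of antibiotics which, in addition to antibacterial properties, possess potent anti-inflammatory properties and also influence bacterial biofilms". Of the two earlier trials described in 3.4.2, the favourable one tested a different macrolide: "clarithromycin was effective in reducing the length of hospital stay, severity of illness (oxygen use) as well as readmission rate". Those are the outcomes of this trial too: length of stay is primary, and oxygen time and readmission within 6 months are secondary (section 4.8).

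Section 3.4.2 also says of azithromycin: "Once weekly dosing has been shown to be sufficient for tissue effects lasting over a week". On local use it says: "azithromycin is currently widely used in the Northern Territory for bronchiectasis, trachoma and sexually transmitted diseases".

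Section 4.6 leaves all other care to the attending physician. Section 4.3 plans 100 infants in total and states that 23 per group are needed to detect a 24 h difference in mean stay with 90% power at alpha 0.05.

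**The concern.** An exclusion for recent drug use is there to keep the comparator free of the action under test. Here that action is described as belonging to a class, but the exclusion names one member of it. Read literally, section 4.1 admits an infant who is taking clarithromycin on the day of enrolment. If allocated to placebo, that infant already has some of the effect the trial seeks. If allocated to azithromycin, the infant may have less left to gain.

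At stake is the contrast in length of stay and oxygen time, which would shrink towards zero in proportion to the share of such infants. If the last macrolide and its date are not recorded, the analysis could not examine this afterwards.

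**Working it through.** **Step 1: does any other section close the gap?** The contraindication criterion in 4.1 concerns suitability for the drug, not exposure to it. Sections 4, 4.2 and 4.2.1 add no screen for prior macrolides. Section 4.6 does not restrict other treatment. The gap is therefore open on the text.

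**Step 2: which arm is affected?** Prior use precedes randomisation, so in expectation the same share q of exposed infants enters each arm. Suppose prior exposure gives the full effect and the study dose adds nothing for those infants. The azithromycin mean is then unchanged, the placebo mean improves by 24q hours, and the difference becomes 24(1 − q). If exposure gives only a fraction r of the effect, the difference is 24(1 − qr), which is a smaller loss.

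**Step 3: the plan's own figure.** Section 4.3 gives the difference (24 h), alpha and power but no SD, so 23 per group cannot be reproduced from the stated inputs. Solving backwards with the two-sided normal formula n = 2(1.960 + 1.282)² × SD² / 24² gives 23 for an SD of about 24.6 to 25.1 h (27.2 to 27.8 h if one-sided). With SD = 25: 2 × 10.51 × 625 / 576 = 22.8, rounded up to 23. I use 25 h below as an implied value.

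**Step 4: dilution and power.** Power is Φ(δ / (SD × √(2/n)) − 1.96). With SD 25, the standard error is 7.37 h at 23 per arm and 5.00 h at 50 per arm (100 infants, assuming 1:1). The values of q are assumptions, and full effect from prior exposure is taken as the worst case.

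| Assumed q | Difference 24(1 − q) | Power, 23 per arm | Power, 50 per arm | n per arm for 90% |
|---|---|---|---|---|
| 0 | 24.0 h | 90.2% | 99.8% | 23 |
| 5% | 22.8 h | 87.1% | 99.5% | 26 |
| 10% | 21.6 h | 83.4% | 99.1% | 29 |
| 20% | 19.2 h | 74.0% | 97.0% | 36 |

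Example, q = 10% and 50 per arm: 21.6 / 5.00 − 1.96 = 2.36, and Φ(2.36) = 99.1%.

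**Step 5: sensitivity to the SD.** The cushion at 50 per arm depends on the implied SD. At an assumed SD of 36 h, the standard error is 36 × √(2/50) = 7.2 h. Power is then Φ(24/7.2 − 1.96) = Φ(1.37) = 91.5% without dilution, and Φ(21.6/7.2 − 1.96) = Φ(1.04) = 85.1% at q = 10%.

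Section 4.8.1 also plans separate analysis within Indigenous status. If the two groups were equal in size (an assumption), each would have about 25 per arm, close to the 23-per-arm column. The planned analysis is non-parametric, so these normal-theory figures are indicative only.

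**The case against.** The strongest case against runs as follows.

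- **No evidence of exposure.** The documents report no use of clarithromycin or any other macrolide in infants at either site. Section 3.4.1 says most children with bronchiolitis at the Darwin hospital receive antibiotics, but names no class. This stands. The size is unknown and may be close to nil.
- **The comparison is azithromycin against placebo on top of usual care.** Section 3.2 tests a single azithromycin dose, and 3.4.2 distinguishes azithromycin from clarithromycin in half-life and tissue penetration. This stands in part. The drugs are not treated as interchangeable, but the protocol still credits the action to the class and relies on the clarithromycin result. It already excludes recent azithromycin, so it accepts the principle. It is also true that a wider entry criterion would not stop macrolides being given after enrolment, which 4.6 leaves open.
- **Randomisation protects the comparison.** This stands as regards bias. It does not prevent dilution.

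Several stronger readings are tempting but not supported:

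- A reader might infer that the 7-day window is plainly too short because 3.4.2 speaks of effects beyond a week. That sentence explains a weekly dosing interval and does not quantify the excess over 7 days. The two statements need reconciling, but they do not show that the window is wrong.
- A reader might take the remark on wide regional use as evidence of frequent exposure. It names bronchiectasis, trachoma and sexually transmitted diseases. The chronic lung disease exclusion should remove the first, and the last is an unlikely indication at 18 months or less.
- A reader might say that earlier macrolide use contaminates the pre-dose swab. The swab records the infant's true state before study drug, so earlier use is a baseline characteristic.

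**Conclusion.** The point holds as an inconsistency between the eligibility criteria and the rationale. Section 4.1 excludes recent azithromycin but not recent or current use of another macrolide, while 3.1 and 3.4.2 credit the tested action to the class. The consequence is dilution towards no difference, with no directional bias.

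Its size cannot be fixed from the protocol. Under the worst case of full prior effect, each 10% of placebo infants affected takes 2.4 h off the 24 h difference. At about 50 per arm the loss of power is small if the SD is near 25 h: from 99.8% to 99.1% at an assumed 10%. It would matter more with a larger SD or in the separate analyses by Indigenous status. The conclusion about the text does not depend on these assumptions; the figures do. Minor severity, worth correcting because it is cheap.

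**What to change.** In section 4.1, change the recent-use exclusion from azithromycin to any macrolide. Record at enrolment the last macrolide received and its date. The enrolment form is not among the documents, so if it already has this item, nothing needs adding. The sponsor should also reconcile the 7-day window in 4.1 with the duration of tissue effect claimed in 3.4.2, using the source cited there; no particular window is proposed here.

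The cost is one eligibility line in an amendment, at most one form item, and perhaps a few recently treated infants lost to recruitment.

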### 4.2 Enrolment protocol

Plain-language educational tools will be used to explain the study to the primary caregiver of a clinically eligible infant. If informed consent is given the infant will be enrolled and randomised to receive either a single, oral dose of azithromycin syrup at 30mg per/kg or an equivalent volume of placebo (syrup).

#### 4.2.1 Enrolment procedure

1. After obtaining informed consent, complete a consent form and give a copy of this and the information sheet to the carer.
2. Complete the enrolment form and the as much of the demographic and medical history as possible from the carer.
3. Use the date of birth and Indigenous status data to determine the treatment strata. There are 4 possible strata
  - Strata 1** Indigenous 6 months and less
  - Strata 2** Non Indigenous 6 months and less
  - Strata 3** Indigenous older than 6 months
  - Strata 4** Non Indigenous older than 6 months
4. Complete a chart notification sticker and stick in the child's medical chart

#### 4.2.2 Randomisation and blinding of treatment allocation

This is a double-blind, randomised, placebo-controlled trial with concealed allocation. The study medications will be assigned the labels A, B, C or D (two labels assigned to placebo azithromycin and two assigned to azithromycin) by an independent person of the study at Menzies School of Health Research. Neither the study team (researchers, hospital staff) nor parents will know which treatment group (placebo or azithromycin) the infant has been assigned until the results have been analysed. Placebo azithromycin has been specifically manufactured by IDT Australia Limited (Melbourne, Victoria) and has a similar smell and taste to active azithromycin. The manufacture of placebo was

primarily for our NHMRC funded international study on bronchiectasis in Indigenous children.

The treatment allocation list has been computer generated by using stratified block randomisation. There are 4 sheets, each corresponding to the treatment strata. Treatment allocation has been concealed by black sticker. Upon enrolment an infant will be assigned to the next treatment on the appropriate stratified list and the treatment (A, B, C or D) revealed.

**Procedure:**

1. After identifying the correct strata write the child's name and HRN on the next available line. The number refers to the child's study identification number.
2. Remove the sticker to reveal the study medication allocation (letter A, B, C or D). Record this on the child's chart notification sticker and on the enrolment form.
3. Treating physician to complete ABIS script to order medication/placebo on medication chart (dose 30mg/kg). Medication scripts are found in the study documents and are given to physician by ABIS study staff.
4. ABIS script taken to pharmacy by ABIS study staff and medication dispensed.
5. Take medication back to the paediatric ward and inform the nurse looking after the child that the child has been enrolled in the study.
6. For children enrolled on the weekends, please ensure that scripts are taken down to the Pharmacy before 1000hrs to ensure the pharmacy has enough time to dispense. Administer/supervise administration of first dose of medication.

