#### **4.3 Study size**

We plan to enrol 100 infants total. Children will be stratified by age (6 months and less and over 6 months), Indigenous status (Indigenous and non Indigenous) and site (Darwin and Townsville). The mean length of stay for bronchiolitis at Royal Darwin Hospital is 96 hours. To detect a mean difference of 24 hours in length of stay between treatment groups with an alpha of 0.05 and a power of 90%, the required sample size is 23 infants per group.

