#### 4.6 Clinical assessment

Children enrolled in this study will be managed by hospital staff according to standard clinical practice for the management of bronchiolitis. They are not exempt from receiving any care or management protocol specified by the attending physician.

A standardised sheet will be used to collect clinical data. Demographic information and medical history will be obtained from the primary care-giver and from hospital records. The primary and secondary outcome measures (described below) will be monitored from the medical chart until the acute study end-point has been reached (defined as >16 hours off supplemental oxygen and infant is feeding well). Clinical assessment data includes oxygen requirement and level, physiological measurements for clinical severity score (respiratory rate, accessory muscle use, degree of wheeze), other physiological measurement (temperature, heart rate), requirement for other therapies (IV fluids, nutrition, antibiotics). In addition routine investigatory parameters (FBC and chest x-ray findings) will be recorded.

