### 6.2 Methods of assessing safety parameters

Side effects of Azithromycin are rare. Those listed in MIMS Annual 2001 included: nausea, vomiting, diarrhoea, or abdominal pain. Rare but potentially serious side effects listed are angioedema and cholestatic jaundice.

The children enrolled in the study have been admitted to TTH and RDH and as such are monitored according to hospital protocol. The child's progress is monitored daily by the study staff via the medical chart and the Nursing Unit Manager.

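### The shared treatment letter (A to D) is written on a sticker in the medical chart, so a guess or unmasking for one infant carries to all infants with that letter; the unique study number would serve instead

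*Protocol*

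**What the plan says.** Section 4.2.2 describes a double-blind trial in which neither researchers, hospital staff nor parents are to know the treatment group until the results have been analysed. The coding scheme is: "The study medications will be assigned the labels A, B, C or D (two labels assigned to placebo azithromycin and two assigned to azithromycin". An independent person assigns the labels, and the placebo is described as similar in smell and taste.

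The numbered procedure under 4.2.2 then gives each infant a unique study number from the allocation sheet (step 1). In step 2 the letter is uncovered and copied to two places, the sticker and the enrolment form: "Remove the sticker to reveal the study medication allocation (letter A, B, C or D). Record this on the child's chart notification sticker", and the same sentence goes on to name the form. The fourth step of 4.2.1 says where the sticker goes: "Complete a chart notification sticker and stick in the child's medical chart".

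The chart is a working document for two groups.
- **Hospital staff.** Section 4.6: "Children enrolled in this study will be managed by hospital staff according to standard clinical practice for the management of bronchiolitis".
- **Study staff.** Section 4.6 says the primary and secondary outcomes "will be monitored from the medical chart until the acute study end-point has been reached", and section 6.2 adds: "The child's progress is monitored daily by the study staff via the medical chart and the Nursing Unit Manager".

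The primary outcome is length of stay, and the first secondary outcome is time on supplemental oxygen (4.8). Section 4.3 states: "We plan to enrol 100 infants total", at two sites.

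**The concern.** A code seen by the people who manage and assess the infants should identify one infant only. Here it identifies a quarter of the trial. If a nurse or data collector comes to associate a letter with active drug or placebo, the belief attaches to every past and future infant with that letter. Section 6.2 lists gastrointestinal effects for azithromycin, so there is something to notice, and the letter in the chart allows such observations to be grouped.

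At stake are two outcomes that ward decisions can influence. Even the acute end-point in 4.6, a fixed period off oxygen plus feeding well, contains a judgement about feeding. A belief about a letter could affect the timing of weaning or discharge, or how an adverse event is attributed. No analysis plan can restore blinding lost during care.

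**Working it through.** The protocol gives no figure on this point to reproduce. The inputs are 100 infants (4.3), four letters with two per product (4.2.2) and two hospitals (4 and 4.3). Equal use of the letters and equal enrolment by site are assumptions; the protocol states neither.

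**Step 1: infants per letter.** 100 / 4 = 25. Per ward, 25 / 2 = 12.5, taken below as 12.

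**Step 2: reach of one unmasking.**
- One letter unmasked: the product is certain for 25 infants. Of the other 75, 50 are on the other product, so guessing that product for all of them is right for 50. In total 25 + 50 = 75 of 100 are classified correctly.
- Both letters of one product unmasked: all 100 are known.
- Unique study number in place of the letter: one infant is revealed.

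**Step 3: how easily a pattern would appear.** Let each letter's event count be binomial, with n infants and rate a (active) or p (placebo). The letters rank correctly if both active counts exceed both placebo counts:

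P = Σₖ [F(k)² − F(k−1)²] × [1 − G(k)]²

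Here F is the binomial(n, p) distribution function and G the binomial(n, a) one. All rates are assumed, because the protocol gives none.

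| Assumed rates (active v placebo) | n = 12 | n = 25 |
|---|---|---|
| 3% v 1% | 7% | 18% |
| 6% v 2% | 18% | 32% |
| 15% v 5% | 38% | 60% |
| 30% v 10% | 62% | 85% |
| 10% v 10% (no difference) | 9% | 11% |

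The n = 12 column is the relevant one for a single ward, and it is reached only when that ward's last infant has been enrolled. Halfway through, at n = 6, the probability is 2.5% at 3% v 1%, 23% at 15% v 5% and 40% at 30% v 10%.

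The top row is low because there is little to see. Expected events on one ward over the whole trial are 2 × 12 × 0.03 + 2 × 12 × 0.01 = 0.96, about one event across all four letters.

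**Step 4: from pattern to bias.** Nothing in the protocol allows this to be put in hours. It gives no basis for how far a belief about a letter would move discharge, so no shift in length of stay is estimated.

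**The case against.** The case on the other side is substantial, and most of it limits the size of the problem.

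- **No contradiction.** A reader might infer that the chart sticker breaks the blinding promised in 4.2.2. The text does not support that. The promise concerns knowledge of the treatment group, not sight of a coded letter. Two letters per product and an independent code holder are real safeguards: staff would have to work out both which letters pair and which pair is active. This stands.
- **Side effects are described as rare.** Section 6.2 says so just before its list. A reader who saw only the 62% or 85% above might conclude that the blind is likely to fail. Those figures need event rates well above anything that wording suggests, and the 85% also needs an observer who sees both wards at the end of the trial, when no discharge remains to be influenced. This stands.
- **Correct ranking is not unblinding.** The probability says only that the counts fall in the right order. Staff would have to tally by letter, and would not know that their ranking was right. This stands.
- **Who decides is not spelled out.** The protocol does not name who weans oxygen or discharges. That hospital staff do so is an inference from 4.6, though a natural one.
- **Removing the letter from the chart does not hide it from everyone.** Whoever uncovers the allocation sees it, and the allocation sheet shows letters already opened in that stratum. This stands, and limits what the fix can achieve.

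None of this gives a reason for the letter to be in the chart. No section shown uses it there, although the adverse-event flowchart (6.3) is not visible, and step 1 already supplies a unique identifier.

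**Conclusion.** The point holds as a cheap improvement. Followed as written, the procedure puts a code shared by about 25 infants (about 12 per ward) into the record used by those who manage the infants and those who collect the outcomes. The blind is weaker than it need be, because one suspicion or unmasking spreads to every infant with that letter. It is not direct unblinding, and the documents do not show that bias would follow.

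The 25 and 12 rest on equal use of the letters and equal enrolment by site. The chance that event counts would point the right way on one ward runs from about 7% to 62% over the assumed rates, and the protocol's own description of side effects favours the lower end. Confidence is high that the letter is in the chart and shared, and low on how much this would matter in practice.

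**What to change.** Amend step 2 of the procedure in 4.2.2, and the sticker and enrolment form with it:

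1. Write only the study identification number on the chart sticker and the enrolment form.
2. Keep the letter on the allocation sheet, and pass it to pharmacy on the study's dispensing request, which is not filed in the chart. Steps 3 and 4 should say that the letter does not appear on the medication chart; at present they are silent on this.
3. Have pharmacy label the dispensed dose with the study number in place of the letter.
4. Where existing staffing allows, have outcomes abstracted by study staff who did not open that infant's allocation.

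The cost is a change of wording and a small labelling step in pharmacy, which already dispenses each dose. Traceability is kept, because the study number leads back to the allocation sheet. What remains is that the study member who reveals the allocation still sees the letter; item 4 reduces that exposure but does not remove it.
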